### Statistical analysis

The primary analysis will follow the intention to treat principle, i.e. the participants will remain in the group they were randomized to and not analyzed according to the interventions actually received.

Child-specific composite test scores at the end of the third academic year will be compared between intervention and control groups using an analysis of covariance (ANCOVA) model. Stratification factors included in the randomization (and no others) will be adjusted for in the primary analysis. Provided normality assumptions hold, robust standard errors, allowing for the clustering, will be used here and elsewhere. Bootstrap confidence intervals will be reported if the normality assumptions are seriously violated. The adjusted difference in means will be divided by the SD of the test score in the control group to give a standardized difference, with a non-parametric bootstrap confidence interval (bias corrected and accelerated, 2000 replications) computed for this.

Secondary analyses will extend the ANCOVA model described above to (separately) investigate interactions by ethnic group, gender, wealth and geographic location. Sensitivity analyses will examine the effect on the treatment effect estimate of different treatment of missing data: e.g. imputation, assigning all missing values a zero, and other specifications according to Manski [9]. Program cost per 0.1 SD improvement in test scores will be calculated.

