## Methods

### Study population and eligibility

This will be a cluster-randomized controlled trial conducted in eligible villages in the Lower River and North Bank Regions of The Gambia, which is located in West Africa. A village will potentially be eligible if the following conditions are met:The number of households in the village is between 15 and 300 according to the 2013 Gambian census;There are at least 15 children eligible for inclusion in the trial at the time of our enumeration^3^;It falls inside an eligible cluster, determined by an enumeration and mapping exercise described below, designed to minimize the risk of bias from contamination;The *Alkalo* (village chief) consents to allow the village to participate in the trial.

A child will be eligible if he or she is resident in a village within an eligible cluster, and fits the following criteria:He or she did not attend first grade or higher in a lower basic school or madrasa in the 2014–2015 academic year;The child’s caretaker intends to enroll the child in the first grade in the 2015–2016 academic year;He or she is born between 1 September 2007 and 31 August 2009;The caretaker consents to allow the child to participate in the trial.

Participants will be informed that they may withdraw from the trial at any time.

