### Sample size calculations

According to the regional directorates of the MoBSE in the Lower River and North Bank Regions [16], just under 10,000 grade 1 children are eligible to attend school in the combined North Bank and Lower River regions in the 179 public schools in these regions. The exact numbers of clusters and eligible students will not be known until after the first enumeration is carried out, but based on the above numbers we estimate that there will be around 150 clusters, each including an average of 40 students (6000 students in total). In the STRIPES trial the estimated effect was a 0.75 SD increase in mean score: however, effects of smaller magnitude than this would still be important to detect. Assuming that 60 % of the eligible children will take the test at the end of the trial and an intra-cluster correlation coefficient of 0.23 (as seen in the STRIPES trial), then a trial with 75 intervention villages and 75 control villages will give over 90 % power to detect a difference of 0.3 SD in the standardized score between intervention and control villages^5^ using a conventional 2-sided significance level of 5 %. If the treatment effect is of the order of that seen in the STRIPES trial then there will be reasonable statistical power to explore interactions by ethnicity, gender, wealth and geographic location.

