### Assignment of interventions

Randomization of clusters will be performed by the trial statistician based in London using a random number generator. Randomization will be stratified by region (North Bank versus Lower River) and by above/below median distance to the main highway in each region. This is an unblinded study as, following randomization, participants will be aware of whether or not they are in an intervention or control village. Participants will be enrolled by the trial’s research arm, which will conduct all enrollment and data collection operations. This research arm will be operated entirely independently of the team delivering the intervention in the intervention group.

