### Data collection, entry, and management

In all eligible villages we will collect the following information:Individual-level information about the parents/guardians of eligible children and about the children themselves at the beginning of the trial, child-level information at the end of the first and second academic years, and child, sibling, and parent/guardian-level information at the end of the trialThe performance of eligible children on an EGRA/EGMA examination^6^, administered at the end of the trial, and on the National Third Grade Assessment ExaminationVillage-level information on the access to various facilities and amenities in each eligible villageSchool-level information about the school facilities and teachers, including attendance at school, observed during the course of the trial, of both students and teachers

Tests will be administered to all eligible children available in the village on the day of testing. In some cases, if a holiday, strike, or administrative necessity negatively impacts attendance at the test, a second visit to that village to reach all eligible and available children will be conducted.

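### The primary model excludes every covariate except the randomization strata; a short fixed baseline list would be a cheap improvement, mainly against selective test attendance

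*Protocol article*

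**What the plan says.** The Statistical analysis section sets an ANCOVA of the composite score at the end of the third year and closes the covariate set: "Stratification factors included in the randomization (and no others) will be adjusted for in the primary analysis". The strata are given under Assignment of interventions: "Randomization will be stratified by region (North Bank versus Lower River) and by above/below median distance to the main highway in each region". That makes four cells.

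Other baseline information exists. The Data collection section lists "Individual-level information about the parents/guardians of eligible children and about the children themselves at the beginning of the trial". Birth date has to be known to apply the eligibility rule: "He or she is born between 1 September 2007 and 31 August 2009". By the Participant timeline, enumeration and enrolment (January to July 2015) come before randomization. The Endpoints section names gender, ethnic group and parents' education as individual-level subgroup factors, without saying when they are recorded. The EGRA/EGMA test is listed only at the end of the trial.

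On attendance, the Sample size section works on this basis: "Assuming that 60 % of the eligible children will take the test at the end of the trial". The Data collection section calls finding and motivating children for the test the main challenge, above all in children not receiving the intervention. Imputation, zero assignment and Manski-type specifications are planned as sensitivity analyses.

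**The concern.** The article does not leave covariates to a later plan; it rules them out of the primary model. A later analysis plan could add them to that model only by departing from the protocol.

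The stake is mainly bias. A strata-only comparison of tested children is unbiased if, within arm and stratum, absence from the test is unrelated to the score. The article itself plans for 40% absence and expects more difficulty in one arm. Age, gender, ethnic group and parents' education are plausible predictors both of the score and of who attends. With them in the model, absence need only be unrelated to the score given those variables as well.

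Precision and chance imbalance between clusters are the second stake. In a linear model the adjusted difference targets the same quantity. The article divides it by the control-group SD of the test score, so the reported scale need not change.

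**Working it through.** **Inputs from the Sample size section.** 75 clusters per arm, on average 40 children each, 60% tested (40 × 0.60 = 24 per cluster), intra-cluster correlation 0.23, difference 0.3 SD, two-sided 5%.

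**Step 1: the plan's own figure.** The article says "a trial with 75 intervention villages and 75 control villages will give over 90 % power to detect a difference of 0.3 SD".
- Design effect = 1 + (24 − 1) × 0.23 = 6.29.
- Effective size per arm = 75 × 24 / 6.29 = 286.2.
- SE = √(2/286.2) = 0.0836.
- Power = Φ(0.3/0.0836 − 1.96) = 94.8%. A noncentral t on 148 df gives 94.6%.

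The stated power is reproduced with no added covariates.

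**Step 2: where the variance lies.** The variance of a cluster mean is 0.23 + 0.77/24 = 0.2621. The between-cluster share is 0.23/0.2621 = 88%, leaving 12% within clusters.

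**Step 3: precision gain.** Let Rb and Rw be the shares of between- and within-cluster variance explained by the added covariates. Then SE² = 2 × [0.23(1 − Rb) + 0.77(1 − Rw)/24]/75. The article gives no R², so 5%, 10% and 20% are assumptions. Equivalent extra clusters = 150 divided by the ratio of new to old SE², minus 150.

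| Assumed R² | Acts at | SE | Fall in SE | Extra clusters | Power at 0.3 SD |
|---|---|---|---|---|---|
| 5% | within only | 0.0833 | 0.3% | 0.9 | 94.9% |
| 10% | within only | 0.0831 | 0.6% | 1.9 | 95.1% |
| 20% | within only | 0.0826 | 1.2% | 3.8 | 95.3% |
| 5% | both levels | 0.0815 | 2.5% | 7.9 | 95.7% |
| 10% | both levels | 0.0793 | 5.1% | 16.7 | 96.6% |
| 20% | both levels | 0.0748 | 10.6% | 37.5 | 98.0% |

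Nearly all the gain depends on the covariates explaining differences between villages.

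**Step 4: illustration of selective attendance.** All settings here are assumed: true effect 0; 65% tested in the intervention arm and 55% in control; one baseline covariate explaining 5% to 30% of score variance; log-odds slope of 0.5 for being tested on that covariate.
- Same selection in both arms: unadjusted bias −0.01 to −0.03 SD.
- Selection in controls only: −0.05 to −0.12 SD. Against the planned SE, 0.047/0.0836 = 0.6 to 0.119/0.0836 = 1.4 standard errors.
- Adjusted for the covariate: about 0 in both cases.

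The adjusted result is near zero by construction, because selection acts only through the covariate that is adjusted for. The exercise shows what measured selection could do to the strata-only estimate; it does not predict what will happen.

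**The case against.** A pre-specified model adjusted for the randomization strata matches the design, is valid, and reaches its power target unaided. Closing the covariate list also protects against choosing covariates after seeing imbalance, and the Trial status section says that clusters were already randomized in September 2015. All of this stands. It means the list must be chosen blind to balance; it does not mean that there can be no list.

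Four stronger readings are tempting, and the article does not support them:
- *The analysis is wrongly called ANCOVA, or drops a baseline score.* No baseline test is listed, so there is no score to include.
- *Missing outcomes are left unaddressed.* Imputation and Manski-type analyses are planned, and the Data collection section describes yearly tracking meetings, recompense and a common test site. Manski-type specifications do not rely on measured covariates. These analyses are sensitivity analyses, however, so the primary estimate itself still rests on the stronger assumption.
- *A gain of 5% to 11% in the SE is established.* It requires covariates that explain variance between villages as well as within them. Age and gender probably vary mostly within villages. Ethnic group and parents' education may differ between villages, but the article gives no figure.
- *All four covariates are known to be held before randomization.* Only birth date is clearly required by then. For the others this is a reasonable inference from the baseline data collection and the subgroup list.

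Supporting adjusted analyses may also stand in an analysis plan that is not shown, so their absence from the article is not the point. The explicit exclusion from the primary model is.

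**Conclusion.** The point holds as a recommended improvement. The strata-only model is neither invalid nor underpowered.

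The firmer ground is attendance: with 40% expected untested and controls expected to be harder to test, a fixed baseline list makes the primary estimate depend on a less demanding assumption. It helps only for measured predictors that are reasonably well modelled; unmeasured causes of absence remain, and the planned sensitivity analyses are still needed for them.

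The precision gain runs from negligible (about 0.3% to 1.2% of the SE) to modest (2.5% to 11%), depending on an assumed R² of 5% to 20% and on the level at which it acts. The bias figures rest wholly on assumed attendance patterns. The existence of the exclusion is certain; the size of the benefit is not.

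**What to change.** In the Statistical analysis section, replace the parenthesis that bars other covariates with wording such as: *The primary model adjusts for the stratification factors and for the following covariates measured before randomization: child's age and gender, and ethnic group and parents' education where recorded at baseline. The list was fixed without reference to balance by arm or to outcome data. The model with stratification factors only is a sensitivity analysis.* State a simple rule for missing covariate values (a missing-value indicator or mean value), keep the control-group SD of the test score as the divisor, and use the same list in the planned imputation model.

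No new data collection is needed, and the test is not due until 2018. The cost is a protocol modification, communicated to the ethics committee and each consent level as the Ethics and dissemination section requires, plus a check of which covariates were in fact recorded before randomization. Because randomization has taken place, the covariates should be chosen by someone who has not seen baseline data by arm.

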### Monitoring

As we anticipate no potential harms from this intervention, there will be no Data Monitoring Committee, interim analyses or stopping rules.

### Ethics and dissemination

Ethical approval for this study has been obtained from the London School of Hygiene and Tropical Medicine (LSHTM) Interventions Research Ethics Committee, approval dated 27 November 2014, ethics reference number 8767. Consent will also be obtained at the following levels:The national government level, from the MoBSE of The GambiaThe village level, from each village’s *Alkalo*The household level, from the household head in each household where data are collectedThe caretaker level, from the caretaker of each eligible child

Any protocol modifications will be communicated to the LSHTM Ethics Committee and each consent level and consent will be re-obtained at the village and parent level at that point if deemed necessary by the LSHTM Ethics Committee.

All data will be kept strictly confidential – names will be removed from the database before analysis and the paper data collection instruments will be kept in a secure location in Banjul and destroyed after the statutory period expires.

We will disseminate the results of the trial to all enrolled villages and to the MoBSE through in-person meetings and delivery of study summary documents.

### Administrative structures

The trial will be run by independent research and implementation teams and supervised by a Trial Steering Committee. The trial will be jointly managed by the Field Research Manager, the Project Manager from the implementation team, and Effective Intervention senior staff.

### Implementation team

The team responsible for managing and implementing the education intervention will consist of:Para-teachers who will teach the remedial lessons to a group of 20 to 30 eligible children in each eligible villageMonitors who will support the para-teachers’ work, monitoring their performance and evaluating children’s learning outcomesA Technical Team who will develop strategies, conduct trainings, and periodically supervise the work of para-teachers, monitors and children’s learning outcomesA Project Manager and several Project Officers who will coordinate and support all the work in the villages.

### Research Team

The team responsible for collecting the data that will evaluate the effectiveness of the project will consist of:Enumerators who will administer surveys to enroll children in the study and collect data from children’s familiesSupervisors who will lead field research teams in the field, supervising and facilitating the work of enumerators. They will also obtain consent from village *Alkalos* and school headmastersA Research Officer who will be responsible for monitoring teams (supervisors and fieldworkers) and facilitating and managing all data collection effortsA Field Research Coordinator who will lead the team and direct research activitiesTest AdministratorsData Entry Operators who will enter the data received from the fieldA Data Entry Supervisor who will supervise data entry, printing of forms, and error management

## Discussion

Economic evaluation and sustainability of measures after intervention: along with the overall impact of the intervention, we will conduct a cost-effectiveness analysis in which we calculate the program cost for 0.1 SD improvement by the intervention.

Ethics/protection of human subjects: other than the consent processes discussed above, there are no major ethical issues for this study.

## Trial status

Clusters were randomized in September 2015 and the intervention is due to start January 2016.

## Abbreviations

ANCOVA: analysis of covariance
ASC: after-school classes
GDP: gross domestic product
LSHTM: London School of Hygiene and Tropical Medicine
MoBSE: Ministry of Basic and Secondary Education
NGO: non-governmental organization
RCT: randomized controlled trial
SD: standard deviation
STRIPES: Support To Rural India’s Public Education System
SMC: School Management Committee
TLM: teaching and learning materials
UNICEF: United Nations Children’s Fund
VDC: Village Development Committee.
